## Other Assessments

Summary of measures by assessment point

**SCL-10 (Symptom check list -10)**

A tool used to uncover psychiatric symptoms of depression and anxiety. The questionnaire is translated to Norwegian and validated in a Norwegian population^23^.

**Time-Line Follow-back**

A visual tool helping patients to remember events the previous 30 days ^24^.

**Alcohol Craving Experience Questionnaire (ACE)**

One of the most used tools to measure craving of alcohol ^25^. There is no Norwegian translation available; therefore this questionnaire has been translated into Norwegian by our research group for this purpose before study start.

**PAM-13 (Patient activation measure -13)**

13 questions measuring the patient’s ability to acknowledge and take control of own health issues. The questionnaire is translated to Norwegian and validated in population with both chronic disease and pshyiatric disorders ^26,27^

**Tests performed on computer approximately 40 minutes after administration of nasal spray:**

**RMET (Reading the mind in the eye test)**

Contains 36 images of the eye region of different faces. Patients will try to find the corresponding word by choosing between four response options for each image. We used a split version. Day 2: 18 pictures, day 3: 18 pictures, day 30: 36 pictures. ^28,29^

**Dot-probe test**

A test used to measuring attentional bias. Patients look at different face pairs comprising an emotional face (angry or happy) paired with a neutral face for a duration of 500 ms, before a probe replaces the location. Participants will try to press a key on the keyboard that correspond to the location of the probe as soon as possible after it appears. The tes tis repeated on day 2, day 3 and day 30. ^30,31^

**AUDIT (alohol use disorder identification test)**

A 10-item screening tool developed by the World Health Organization (WHO) to

assess alcohol consumption, drinking behaviors, and alcohol-related

problems. Patients will be nterviewed on the phone at Day 60 regarding the last 30 days.^32^

# Safety MONItoring and reporting

The investigator is responsible for the detection and documentation of events meeting the criteria and definition of an adverse event (AE) or serious adverse event (SAE). Each patient will be instructed to contact the investigator immediately should they manifest any signs or symptoms they perceive as serious.

The methods for collection of safety data are described below.

## Definitions

### Adverse Event (AE)

An AE is any untoward medical occurrence in a patient administered a pharmaceutical product and which does not necessarily have a causal relationship with this treatment.

An adverse event (AE) can therefore be any unfavorable and unintended sign (including an abnormal laboratory finding), symptom, or disease temporally associated with the use of a medicinal (investigational) product, whether or not related to the medicinal (investigational) product.

The term AE is used to include both serious and non-serious AEs.

. If an abnormal laboratory value/vital sign are associated with clinical signs and symptoms, the sign/symptom should be reported as an AE and the associated laboratory result/vital sign should be considered additional information that must be collected on the relevant CRF.

### Serious Adverse Event (SAE)

Any untoward medical occurrence that at any dose:

- Results in death
- Is immediately life-threatening
- Requires in-patient hospitalization or prolongation of existing hospitalization
- Results in persistent or significant disability or incapacity
- Is a congenital anomaly/birth defect
- Is an important medical event that may jeopardize the subject or may require medical intervention to prevent one of the outcomes listed above.

Medical and scientific judgment is to be exercised in deciding on the seriousness of a case. Important medical events may not be immediately life-threatening or result in death or hospitalization, but may jeopardize the subject or may require intervention to prevent one of the listed outcomes in the definitions above. In such situations, or in doubtful cases, the case should be considered as serious. Hospitalization for administrative reason (for observation or social reasons) is allowed at the investigator’s discretion and will not qualify as serious unless there is an associated adverse event warranting hospitalization.

### Suspected Unexpected Serious Adverse Reaction (SUSAR)

Adverse Reaction: all untoward and unintended responses to an investigational medicinal product related to any dose administered;

Unexpected Adverse Reaction: an adverse reaction, the nature or severity of which is not consistent with the applicable product information.

Suspected Unexpected Serious Adverse Reaction: SAE (see section 8.1.2) that is unexpected as defined in section 8.2 and possibly related to the investigational medicinal product(s).

## Expected Adverse Events

Side-effects described by NOMA:

(≥1/10 000, <1/1000): headache, nausea, allergic dermatitis (≥1/1000, <1/100): uterus contractions.

Side-effects by use of Oxytocin are also usual sympthoms patients undergoing detoxification on alcohol are likely to experience. Trained medical staff will observe changes in patient’s wellbeing when monitoring their withdrawal sympthoms, and are available at all times for questions.

Syntocinon nasal spray in the amount used is not known to give any discomfort or known side effects. Half-life of oxytocin is also short; 2-20 minutes. All exess nasal spray will be eliminated in the gastrointestinal channel.

Epileptic seizures, delirium tremens may occur in severe alcohol withdrawal, and will not be considered as a SAE.

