## Recording of Adverse Events

If the patient has experienced adverse event(s), the investigator will record the following information in the CRF:

- The nature of the event(s) will be described by the investigator in precise standard medical terminology (i.e. not necessarily the exact words used by the patient).
- The duration of the event will be described in terms of event onset date and event ended data.
- The intensity of the adverse event: Mild / Moderate / Severe; according to Common Terminology Criteria for Adverse Events version 4.0 (CTCAE).
- The Causal relationship of the event to the study medication will be assessed as one of the following:

Unrelated:

There is not a temporal relationship to investigational product administration (too early, or late, or investigational product not taken), or there is a reasonable causal relationship between non-investigational product, concurrent disease, or circumstance and the AE.

Unlikely:

There is a temporal relationship to investigational product administration, but there is not a reasonable causal relationship between the investigational product and the AE.

Possible:

There is reasonable causal relationship between the investigational product and the AE. Dechallenge information is lacking or unclear.

Probable:

There is a reasonable causal relationship between the investigational product and the AE. The event responds to dechallenge. Rechallenge is not required.

Definite:

There is a reasonable causal relationship between the investigational product and the AE.

- Action taken
- The outcome of the adverse event – whether the event is resolved or still ongoing.

It is important to distinguish between serious and severe AEs. Severity is a measure of intensity whereas seriousness is defined by the criteria in Section 8.1. An AE of severe intensity need not necessarily be considered serious. For example, nausea that persists for several hours may be considered severe nausea, but is not an SAE. On the other hand, a stroke that results in only a limited degree of disability may be considered a mild stroke, but would be an SAE.

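### Section 8.2 denies SAE status to seizures and delirium tremens outright, contradicting the protocol's own outcome-based SAE definition in Section 8.1.2

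*Protocol*

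**What the plan says.** Protocol Section 8.2 (Expected Adverse Events) lists the known side effects of the product and closes with a sentence on withdrawal complications: "Epileptic seizures, delirium tremens may occur in severe alcohol withdrawal, and will not be considered as a SAE".

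Section 8.1.2 defines an SAE by what happens to the patient. Besides death, persistent disability and congenital anomaly, the criteria include:

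- "Is immediately life-threatening"
- "Requires in-patient hospitalization or prolongation of existing hospitalization"
- "Is an important medical event that may jeopardize the subject or may require medical intervention to prevent one of the outcomes listed above"

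On borderline cases, Section 8.1.2 adds: "In such situations, or in doubtful cases, the case should be considered as serious". Its one stated exemption is admission for administrative reasons with no adverse event behind it.

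Section 8.4 says which rule decides: "Severity is a measure of intensity whereas seriousness is defined by the criteria in Section 8.1".

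**The concern.** A site nurse or investigator faced with a withdrawal seizure or delirium has two instructions that can give opposite answers. The reason Section 8.2 offers is that these events belong to severe withdrawal. That may help in judging whether the study drug caused an event, or whether an event was to be expected. It says nothing about whether the event was life-threatening or kept the patient in hospital, which is what seriousness means in this protocol.

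The label has consequences, because several safety procedures are triggered only by SAE status. It also matters for this trial in particular. Section 10.4 treats a reduction in oxazepam as the benefit to be shown, and Section 1.1 names seizures and delirium tremens among the manifestations of withdrawal. These are events a reader would want to see, correctly classified, beside the oxazepam result.

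**Working it through.** The plan gives no figure on this point, so the check is a side-by-side reading.

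**Step 1: is there a contradiction?** Take a delirium tremens that prolongs the inpatient stay.

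| Provision | Answer |
| --- | --- |
| 8.1.1 (AE definition; no causal link needed) | An AE |
| 8.1.2 (prolonged hospitalisation) | Serious |
| 8.4 (8.1 decides seriousness) | Serious |
| 8.2 (closing sentence) | Not serious |

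The same clash arises for an event that is fatal or life-threatening, or for a seizure during the four weeks at home that leads to admission. AE collection starts with study treatment (8.3), and treatment includes those four weeks (5.3). No other section resolves the clash.

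**Step 2: what does SAE status control?**

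- *Reporting to the sponsor.* Section 8.5.1 requires SAEs to reach the sponsor within 24 hours. It sets no such limit for other AEs.
- *Monitoring.* Section 9.3 promises full monitoring of SAEs and the primary endpoint. CRF data in general are source-verified at 20%.
- *SUSAR status.* Section 8.1.3 defines a SUSAR as an SAE that is also unexpected and possibly related to the product. An event that cannot be an SAE cannot be a SUSAR. The authority and ethics committee reports within 7 or 15 days (8.5.2) and the SUSAR-triggered unblinding (8.6) then fall away, even if the investigator thinks the drug may have caused the event.

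**Step 3: what remains?** The event is still an AE (8.1.1). It is recorded with nature, duration, intensity, causality and outcome (8.4), kept in the sponsor's records (8.5.1) and covered in the study report (8.5.4). The protocol names no substitute for SAE handling, such as a category of events of special interest.

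**Step 4: would the clause ever be applied?** The protocol gives no rate for these events. For scale only, assume a true rate p per patient, independent between the 40 patients (Section 4.2). The chance of at least one event is 1 − (1 − p)^40:

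- p = 1%: 1 − 0.99^40 = 33%
- p = 3%: 1 − 0.97^40 = 70%
- p = 5%: 1 − 0.95^40 = 87%
- p = 10%: 1 − 0.90^40 = 99%

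Across this assumed range, meeting the clause at least once runs from a one-in-three chance to near certainty. Not every such event would necessarily meet 8.1.2, so these are chances that the question arises, not that an SAE is misclassified.

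**The case against.** Several things can be said in favour of the clause.

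*Disease-related events are often handled separately.* That is fair, but a provision that waives expedited reporting for such events differs from one that says they are not serious. Section 8.2 does the second.

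*The sentence may be meant only for events caused by withdrawal.* Even so, that is a causality judgement, and the protocol's AE and SAE definitions do not depend on causality. The narrower reading still contradicts 8.1.2.

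*The sponsor evaluates all AEs for seriousness (8.5.1).* True, but it would do so under the same clause and without the 24-hour limit.

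Three stronger readings are tempting, and the documents do not support them.

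- *A reader might infer that these events would go uncounted, or that an imbalance between arms would stay hidden.* They remain recorded AEs, and a randomised comparison can be made from the AE data. They would be absent from the SAE comparison and might come to notice later.
- *A reader might infer that a favourable oxazepam result could simply reflect under-treated withdrawal.* Oxazepam is triggered by CIWA-Ar score in all patients (7.2), and patients, staff and outcome assessors are blinded (10.2.2). An arm gets less oxazepam because its scores are lower, not because treatment is withheld by arm. The protocol nowhere calls under-treatment the main expected harm.
- *A reader might take the small sample as a measure of the flaw.* Any confidence limit on the event rate is the same whichever label the events carry. Relabelling would not give the trial power to detect an imbalance either: with 20 per arm, 4 against 0 events gives a two-sided Fisher p of 2 × C(20,4)/C(40,4) = 2 × 4,845/91,390 = 0.11, and only at 5 against 0 does it reach 2 × 15,504/658,008 = 0.047.

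**Conclusion.** The contradiction is real and is wrong as written. Section 8.2 removes SAE status from two named events without qualification, while Sections 8.1.2 and 8.4 make seriousness depend on outcome alone.

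Its consequence is limited but definite: slower reporting to the sponsor, lighter monitoring, a closed route to SUSAR status and an incomplete SAE comparison. It does not remove the events from the data, and it leaves randomisation, the primary endpoint and its analysis untouched. The conclusion rests on the text alone. It needs no assumption about how often these events occur or whether oxytocin affects them. Because it concerns how potentially life-threatening events are classified, and the repair is simple, it should be corrected.

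**What to change.** Reconcile Sections 8.1.2, 8.2 and 8.4. Delete the clause in 8.2 that denies SAE status, and state that seizures and delirium tremens are classified under 8.1.2 like any other event.

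They may be described as related to the underlying disease, with their reporting handling stated. They should not be listed as expected reactions to the product. Section 8.1.3 takes its test of unexpectedness from 8.2, so listing them there as expected would keep a possibly drug-related seizure or delirium from ever qualifying as a SUSAR. For the same reason, deletion alone is not quite enough: what is left of the sentence would still sit under a heading about expected events. The amended text should say that the mention concerns the disease and not the product, or should move it elsewhere.

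The cost is a one-sentence amendment, with the usual notification under Section 11.3, and possibly a few more SAE forms. No clinical rule, sample size or analysis changes.

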## Time Period for Reporting AE and SAE

For each patient the standard time period for collecting and recording AE and SAEs will begin at start of study treatment and will continue following the last dose of study treatment is given, because of the short half-life of oxytocin.

During the course of the study all AEs and SAEs will be proactively followed up for each patient; events should be followed up to resolution, unless the event is considered by the investigator to be unlikely to resolve due to the underlying disease. All patients will receive oxytocin or placebo during three days as in-patients supervised by medical staff at all times.

## Recording of Adverse Events

If the patient has experienced adverse event(s), the investigator will record the following information in the CRF:

- The nature of the event(s) will be described by the investigator in precise standard medical terminology (i.e. not necessarily the exact words used by the patient).
- The duration of the event will be described in terms of event onset date and event ended data.
- The intensity of the adverse event: Mild / Moderate / Severe; according to Common Terminology Criteria for Adverse Events version 4.0 (CTCAE).
- The Causal relationship of the event to the study medication will be assessed as one of the following:

Unrelated:

There is not a temporal relationship to investigational product administration (too early, or late, or investigational product not taken), or there is a reasonable causal relationship between non-investigational product, concurrent disease, or circumstance and the AE.

Unlikely:

There is a temporal relationship to investigational product administration, but there is not a reasonable causal relationship between the investigational product and the AE.

Possible:

There is reasonable causal relationship between the investigational product and the AE. Dechallenge information is lacking or unclear.

Probable:

There is a reasonable causal relationship between the investigational product and the AE. The event responds to dechallenge. Rechallenge is not required.

Definite:

There is a reasonable causal relationship between the investigational product and the AE.

- Action taken
- The outcome of the adverse event – whether the event is resolved or still ongoing.

It is important to distinguish between serious and severe AEs. Severity is a measure of intensity whereas seriousness is defined by the criteria in Section 8.1. An AE of severe intensity need not necessarily be considered serious. For example, nausea that persists for several hours may be considered severe nausea, but is not an SAE. On the other hand, a stroke that results in only a limited degree of disability may be considered a mild stroke, but would be an SAE.

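### Section 8.4 lets an alternative cause alone make an adverse event Unrelated, so the causality categories overlap and reactions resembling withdrawal may be under-attributed

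*Protocol*

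**What the plan says.** **The scale (Protocol, section 8.4, Recording of Adverse Events).** The investigator picks a single category: "The Causal relationship of the event to the study medication will be assessed as one of the following". The five options are:

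- *Unrelated*: no temporal relationship to the product, "or there is a reasonable causal relationship between non-investigational product, concurrent disease, or circumstance and the AE".
- *Unlikely*: a temporal relationship, but the product is not a reasonable cause.
- *Possible*: "There is reasonable causal relationship between the investigational product and the AE. Dechallenge information is lacking or unclear".
- *Probable*: the product is a reasonable cause and the event responds to dechallenge; rechallenge is not needed.
- *Definite*: the product is a reasonable cause. Nothing further is asked.

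No order of precedence is given for an event that meets more than one definition.

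**The setting (section 8.2, Expected Adverse Events).** "Side-effects by use of Oxytocin are also usual sympthoms patients undergoing detoxification on alcohol are likely to experience". The listed effects are "headache, nausea, allergic dermatitis (≥1/1000, <1/100): uterus contractions". The same section says that seizures and delirium tremens will not count as SAEs.

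**The SUSAR definition (section 8.1.3).** A SUSAR is an SAE "that is unexpected as defined in section 8.2 and possibly related to the investigational medicinal product(s". An unexpected reaction is "an adverse reaction, the nature or severity of which is not consistent with the applicable product information".

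**The reporting route (sections 8.5.1 and 8.5.2).** Every SAE goes to the sponsor within 24 hours, whatever its causality rating. The sponsor evaluates seriousness, causality and expectedness, and reports SUSARs within 7 or 15 days.

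**The concern.** A causality scale should rise with the strength of the case against the product, and its lowest step should mean that the product has been reasonably ruled out. Here the lowest step can be reached without considering the product at all: a plausible other cause is enough.

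In many trials this would be a small drafting slip. In this one a competing explanation is often close at hand, because patients receive the spray while being detoxified, and section 8.2 itself says the two symptom pictures overlap. Headache and nausea, two of the four listed effects, are also scored items on the CIWA-Ar form in Appendix B.

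What is at stake is safety attribution in the inpatient phase, where section 5.2 sets the larger single dose (6 insufflations, against at most 2 at a time in the outpatient phase). The rating also feeds the SUSAR decision. That decision triggers expedited reporting under section 8.5.2 and unblinding of the patient under section 8.6.

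**Working it through.** No arithmetic applies. The check sets the definitions side by side.

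**Step 1. Which categories fit which event.** Take an event that follows the spray in time, so that the first limb of *Unrelated* is not met. Vary three things that section 8.4 refers to: whether the product is a reasonable cause, whether something else is, and what dechallenge showed.

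| Product a reasonable cause? | Other reasonable cause? | Dechallenge | Definitions met |
| --- | --- | --- | --- |
| No | No | any | Unlikely |
| No | Yes | any | Unrelated, Unlikely |
| Yes | No | lacking or unclear | Possible, Definite |
| Yes | No | event responds | Probable, Definite |
| Yes | No | event does not respond | Definite |
| Yes | Yes | lacking or unclear | Unrelated, Possible, Definite |
| Yes | Yes | event responds | Unrelated, Probable, Definite |
| Yes | Yes | event does not respond | Unrelated, Definite |

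Of the eight rows, six meet more than one definition. In all three rows where both causes are reasonable, the lowest and the highest category are met together. Two assessors could follow the text and place the same event at opposite ends of the scale.

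**Step 2. The order can invert.** An event with no reasonable product cause and no other explanation is *Unlikely* (row 1). An event with a reasonable product cause and a withdrawal explanation may be *Unrelated* (rows 6 to 8). The event with the stronger case against the spray can receive the lower rating.

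**Step 3. The top of the scale.** *Probable* needs a response to dechallenge; *Definite* does not. An event that clearly fails to respond to dechallenge fits neither *Possible* nor *Probable*, so *Definite* is the only positive category left (rows 5 and 8).

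**Step 4. Where causality decides SUSAR status.** A SUSAR must be serious, unexpected and possibly related.

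| Event | What settles its SUSAR status |
| --- | --- |
| Headache or nausea of expected nature and severity | Expectedness: listed in 8.2, so not a SUSAR whatever the causality |
| Allergic dermatitis, uterus contractions | Expectedness as above; neither is a withdrawal symptom in section 1.1 or a CIWA-Ar item |
| Seizure, delirium tremens | The SAE step: 8.2 removes them before causality is asked |
| Tachycardia, psychotic symptoms or agitation, if serious | Causality: section 1.1 names them as withdrawal symptoms and 8.2 does not list them as expected |
| Headache or nausea beyond the expected severity, if serious | Causality |

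The exposed group is the last two rows. For these events everything turns on the words 'possibly related', and at that step the second limb of *Unrelated* is open to the assessor.

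**Step 5. The backstop.** The sponsor's evaluation under section 8.5.1 is a second look at causality. The protocol gives the sponsor no separate scale, and it never says which section 8.4 categories count as possibly related for section 8.1.3.

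**The case against.** A reader might infer that drug reactions during detoxification are unrelated by definition and can never become SUSARs. The documents do not support that.

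- **Permitted, not forced.** An event with a reasonable product cause also meets *Possible*, *Probable* or *Definite*, and another cause does not bar those categories. The text is ambiguous; it does not dictate *Unrelated*.
- **The route stays open.** SAEs reach the sponsor regardless of the investigator's rating, the sponsor judges causality itself, and SUSAR reporting is the sponsor's duty. An investigator's *Unrelated* is nowhere said to be final.
- **The obvious examples fail elsewhere.** Headache and nausea at expected severity drop out on expectedness, and section 8.4 uses severe nausea as its example of an event that is not an SAE.
- **Not every patient has the competing cause.** Section 6.2.1 says only that abstinence symptoms are likely, and section 10.1 gives oxazepam doses starting at 0 mg. A claim about all 40 patients goes too far.
- **A false picture of tolerability is not shown.** Section 8.5.1 records all AEs, section 8.5.4 discusses them without a causality filter, and assessors are blinded (section 10.2.2). How AEs are tabulated by arm can be left to the statistical analysis plan.
- **The *Definite* and *Probable* fault does not change SUSAR status**, since both lie above *Possible*.

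All of these points stand, and they limit the finding. They do not remove it: the definitions overlap, no rule resolves the overlap, and the sponsor's evaluation has no better-defined scale to fall back on. The seizure and delirium tremens exclusion is a separate and absolute block, which correcting section 8.4 would leave in place.

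**Conclusion.** The concern holds in a limited form. Section 8.4 states a defective rule: a reasonable alternative cause is enough for *Unrelated* even when the spray is also a reasonable cause, and *Definite* is easier to meet than *Probable*. The likely result is under-attribution or inconsistent rating of events on days 1 to 3, and possible under-identification of SUSARs among serious, unlisted events that resemble withdrawal.

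This is a risk, not a certainty. How often it would occur cannot be worked out from the protocol, which gives no rate for such events and no rule for choosing between categories. The conclusion assumes that assessors apply the definitions as written and that the sponsor has no other causality scale than the one shown. The efficacy endpoints and sample size are not affected. The wording should be corrected, but the flaw does not undermine the trial.

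**What to change.** 1. In section 8.4, let *Unrelated* apply only when there is no reasonable possibility that the product caused the event. An alternative cause alone should not suffice.
2. Make the five categories mutually exclusive, and give *Definite* a condition stricter than that of *Probable*. Say where an event belongs when dechallenge information is available and negative.
3. In section 8.1.3, state that *Possible* or higher counts as possibly related, and that the sponsor's evaluation in section 8.5.1 uses the same scale.

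The cost is wording in the protocol and the WebCRF. Treatment, visits and sample size do not change. The small downside is a few more events assessed as possibly related.
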